## Methods: participants, interventions, and outcomes

### Study setting {9}

The study will be conducted at the Institute for Interdisciplinary Dermatological Prevention and Rehabilitation at the Osnabrück University (iDerm) [44] in Osnabrück, Germany. The iDerm is an internationally recognised, interdisciplinary healthcare facility, specialising in both inpatient and outpatient individual prevention in occupational dermatology. The institute is recognised for its expertise in interprofessional care of patients with work-related skin diseases (e.g. contact dermatitis, foot eczema, and UV-induced skin cancer [45, 46]), particularly in the areas of diagnostics, therapy, patient education, and counselling.

Patients will be recruited during the 3-week complex inpatient maintenance programme, known as ‘Tertiary Individual Prevention’ (TIP), which has been described and evaluated extensively [33, 47–51]. In short, TIP consists of three phases: the first phase comprises a 3-week inpatient stay at the clinic, during which patients undergo allergy diagnostics and intensive, stage-adapted dermatological treatment. Throughout the inpatient phase, health educational and health psychology interventions (e.g. group educational sessions and individual counselling) are provided to enhance motivation and to promote modification of knowledge, attitudes, and behaviours related to appropriate skin protection, cleansing, and care [40]. Patients also practise and train the recommended skin protection measures under the supervision of occupational therapists at simulated workplace stations [52]. After the inpatient phase, a 3-week post-inpatient period follows, during which patients do not attend work and receive ongoing outpatient dermatological care within the so-called dermatologist procedure [53] to stabilise the treatment effects achieved during the inpatient stay (phase 2). In the third phase, patients return to work under optimised skin protection conditions and, if necessary, continue to receive outpatient dermatological support from their dermatologist [51].

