### Intervention description {11a}

Both the intervention and control groups participate in the standard inpatient individual prevention programme (CAU) at the iDerm. As described above, the programme includes a 3-week inpatient stay at the iDerm followed by a 3-week period of absence from work to facilitate skin stabilisation post-discharge. In week 4 post-discharge, participants return to work with optimised skin protection measures (e.g. optimisation of the use of protective gloves). Participants have access to outpatient dermatological care as needed, either through outpatient physicians or at the iDerm. Standard follow-up appointments, which participants may or may not be able to attend, are typically scheduled shortly before and 4 weeks after returning to work [33, 48, 51].

The intervention group additionally participates in the app-based maintenance programme, which was designed and piloted using a multi-stage, iterative, and user-centred process following the frameworks and recommendations for complex interventions [54, 55]. In this process, patients with WRHE were involved [42, 43]. A goal-setting interview is conducted face-to-face with a health educator on day 16 or 17 of the inpatient stay and lasts approximately 30 min. The interviews follow a semi-standardised protocol—while the key elements are standardised, individual needs and requirements of each patient are considered. During this session, up to five individual skin protection goals for the post-discharge period are collaboratively formulated with the participant and documented within their user profile in the app’s interface. Participants are then registered on the app and familiarised with its functionalities, followed by a test phase until discharge. The maintenance programme begins on the day of discharge (day 21) and continues for 6 months.

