### Outcomes {12}

The desired primary outcome of this study is a change in the participants’ skin protection behaviour, which encompasses the implementation of skin protection measures, cleansing, and care routines in both occupational settings and private daily life. Skin protection behaviour will be measured using a 13-item instrument adapted from the scale used by Matterne et al. [59] and expanded to reflect the content of the skin protection seminars delivered within TIP. The 13 items will be aggregated into a single total score. Items are rated on a 5-point Likert scale; the total score is the mean of all items (higher values indicate better skin protection), with item 11 reverse-coded. The specific items are presented in the Supplementary information (see Additional files 1–3). The primary analysis will compare the change in the mean primary outcome score for each participant from baseline to t4 (6 months after discharge from the clinic) between groups.

The anticipated primary outcome of this study is critical, as adequate skin protection behaviour can have a significant impact on disease course and thus contribute to both the stabilisation of the skin condition and improved disease management in occupational and private settings. Furthermore, it is a commonly used outcome to evaluate the effect of patient education in trials involving patients with WRHE [37, 40, 60].

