The secondary outcome measures are as follows:Skin condition of the hands: self-assessed using the following item: ‘How would you rate the current condition of your skin using a school grading scale?’ (1 = very good, 2 = good, 3 = satisfactory, 4 = sufficient, 5 = poor, 6 = very poor).Skin condition of the hands (clinical-assessed, OHSI [61, 62]): semi-quantitative scoring system for the clinical assessment of hand eczema. Range from 0 to 18. Higher values indicate a worse skin condition.Action control: assessed with a 9-item scale, adapted from Scholz et al. [63]; items rated on a 7-point Likert scale (1 = does not apply at all, 4 = partly applies, 7 = applies exactly). A total score is calculated as the mean of all items (higher scores indicate greater action control). Items and scoring details are provided in Additional file 2.HRQoL: assessed with the Dermatology Life Quality Index (DLQI) [64].Employment status and number of days of sickness-related absence from work (due to the skin condition) during the follow-up period. This self-reported outcome may be influenced by external factors and will be interpreted with appropriate caution. However, no relevant confounding that would impair the comparability between groups is anticipated.

Additionally, in the intervention group only, the following will be assessed:Impact of the MiA app on goal achievement, measured using two items scored on a four-point scale (1 = strongly agree, 2 = rather agree, 3 = rather disagree, 4 = strongly disagree). The items are presented in Additional file 3.Usage behaviour of the MiA app: assessed centrally via usage data collected in the web-based dashboard (so-called Cockpit) over the entire 6-month follow-up period. This includes daily values for tracking skin protection behaviour, daily values for the use of photographic documentation including the number of images (up to four), and related comments.

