## Data collection and management

### Plans for assessment and collection of outcomes {18a}

All data will be collected using paper-based forms. With the exception of the OHSI [61, 62], which is a physician-administered clinical assessment tool for evaluating the severity of hand eczema, all other data will be self-reported by study participants. At baseline, the following sociodemographic data will be collected: age, sex, current occupation, highest educational qualification, employment status, and relationship status. E-Health literacy in the context of medical app usage will also be assessed using the eHealth Literacy and Use Scale (eHLUS) [65]. In addition, primary and secondary outcomes will be assessed at baseline (see ‘Outcomes {12}’). The German-language data collection forms are available from the corresponding author upon request.

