A key advantage of LMMs is their robustness to missing data, which are common in longitudinal studies. Furthermore, LMMs allow the estimation of covariance structures even in studies with relatively small sample sizes, thereby improving the reliability of the results. All analyses will be conducted according to the intention-to-treat (ITT) principle, meaning that all randomised participants will be analysed in the groups to which they were originally assigned, regardless of their level of adherence to the intervention. This approach ensures that the effect estimates reflect the effectiveness of the intervention under real-world conditions. We acknowledge that variation in app usage in the intervention arm may attenuate the observed ITT effect; therefore, app usage will be summarised descriptively, and a pre-specified per-protocol sensitivity analysis will be conducted to assess robustness. To assess the robustness of the results, additional sensitivity analyses will be conducted, including a per-protocol (PP) analysis, which will consider only those participants who adhered to the study protocol as specified. This will include participants who complete all required assessments and, in the intervention group, use the app as specified. Comparing the results of ITT and PP analyses will enable for a more comprehensive evaluation of the stability and reliability of the findings. The significance level is set at *p* = 0.05. An overview of the intended analysis strategies is presented in Table 2.

**Table 2 Tab2:** Overview of planned statistical methods

Category	Outcome	Statistical analyses methods
Primary	Skin protection behaviour	• Statistical model: linear mixed model (LMM) (change t1 to t4)
Secondary	Skin condition of the hands (self-assessed; school grades: ordinal)	• Descriptive: mean value per group and time point • Statistical model: generalised linear mixed model (GLMM)
Secondary	Action control	• Descriptive statistics: mean and standard deviation per group and measurement time • Statistical model: LMM
Secondary	Health-related quality of life	• Statistical model: LMM
Secondary	Employment status	• Descriptive; two-sample *t*-test
Secondary	Sick days due to skin condition	• Descriptive; two-sample *t*-test
Further (intervention group only)	MiA app impact on goal achievement	• Descriptive

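### Table 2 plans a two-sample t-test for employment status, a categorical outcome with no coding defined; sick days should be read alongside a corrected employment result

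*Protocol article*

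**What the plan says.** The Objectives section lists employment status and skin-related sick days among the further objectives. Outcomes {12} defines them together as "Employment status and number of days of sickness-related absence from work (due to the skin condition) during the follow-up period". Table 2, under Statistical methods for primary and secondary outcomes {20a}, gives both rows the same entry, "Descriptive; two-sample" t-test; the second row is labelled "Sick days due to skin condition". The text above the table names the linear mixed model as the preferred method for primary and secondary outcomes, and Table 2 gives the ordinal school-grade item a generalised linear mixed model.

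Plans for assessment and collection of outcomes {18a} lists the baseline sociodemographic items, including "highest educational qualification, employment status, and relationship status". The article gives neither the employment categories nor a rule for turning them into a number.

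On the time window, Intervention description {11a} says of the app programme: "The maintenance programme begins on the day of discharge (day 21) and continues for 6 months". The same section describes the inpatient stay in both arms as "followed by a 3-week period of absence from work to facilitate skin stabilisation post-discharge", and Study setting {9} agrees: "a 3-week post-inpatient period follows, during which patients do not attend work". The article does not say whether those three weeks enter the sick-day count.

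**The concern.** A two-sample t-test compares means. Employment status, collected as a category, has no mean until numbers are assigned to the categories. If those numbers are only labels, the estimated difference, its sign and its p-value follow from the labelling. An effect on employment is a stated objective, and the test as written would not answer it. This is a method that the article states, not a detail left to a later document.

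Sick days raise a related question of interpretation. Absence from work can accrue only while a patient has work. Someone who gave up the job because of the skin disease may report few or no sick days and would count as a good result. The sick-day comparison therefore cannot be read without a sound employment comparison beside it. In addition, part of the follow-up is a planned absence, and its treatment is left open.

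**Working it through.** **Setting.** Two-sample t-test, d = 0.4, two-sided alpha 0.05, power 0.80: 99.08, rounded up to 100 per arm. With 30% dropout, 100 / 0.70 = 142.9, so 143 per arm and 286 in total. The article's N reproduces and does not depend on this point. About 100 per arm is the analysed size used below.

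**Employment status: dependence on the numbering.** The article gives no category frequencies, so these counts are assumed: arm A 70 / 10 / 15 / 5 and arm B 70 / 18 / 4 / 8 over four unordered categories.

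- Chi-square on 3 degrees of freedom. Expected counts in each arm are 70, 14, 9.5 and 6.5. The statistic is 2 × (0²/70 + 4²/14 + 5.5²/9.5 + 1.5²/6.5) = 2 × (0 + 1.143 + 3.184 + 0.346) = 9.35, p = 0.025, whatever the labels.
- Categories numbered 2, 4, 1, 3. Mean A = (70×2 + 10×4 + 15×1 + 5×3)/100 = 2.10. Mean B = (70×2 + 18×4 + 4×1 + 8×3)/100 = 2.40. t-test p = 0.009, A lower.
- Numbered 3, 1, 4, 2. Mean A = 2.90, mean B = 2.60. p = 0.009 again, now A higher.
- Numbered 2, 4, 3, 1. Mean A = 2.30, mean B = 2.32. p = 0.859.

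Over all 24 numberings p ranges from 0.009 to 0.859, and the direction reverses. If the first category were being in work, the proportion is 70/100 in both arms and the risk difference is zero. Some numberings would still give p = 0.009.

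**Employment status coded 0/1.** With 100 per arm and a common true proportion of 0.50, 0.80, 0.90 or 0.95, simulation (20,000 trials each) gave a t-test type I error of 0.054, 0.052, 0.049 and 0.046. The t-test and the uncorrected chi-square reached the same decision every time. The defect therefore depends on the coding, which is not fixed.

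**Sick days: skewness.** Zero-inflated, skewed counts were simulated with 50%, 60% or 70% of patients at zero and a mean of 20, 30 or 15 days in the remainder. The t-test type I error was 0.047, 0.048 and 0.050, so skewness alone does not invalidate the test at this size.

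**Sick days: the planned absence.** It is 21 of 182 days (11.5%). If everyone counts it, each arm's mean rises by 21, since (mean A + 21) − (mean B + 21) = mean A − mean B, and the variances do not change. In the simulation, power was 0.64 with and without the shift.

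**Sick days: leaving work.** Let π be the share of an arm in work and m the mean sick days among those in work. If patients out of work report none, the arm mean is π × m. With equal m in both arms, the arm with the lower π shows the lower mean, so worse job retention appears as fewer sick days.

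**The case against.** The strongest reply is that the employment item may be binary. The categories are not shown, and with a 0/1 coding the t-test does what a chi-square test would do. That stands as a condition, but the article fixes no such coding and lists the item among sociodemographic categories.

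Three stronger readings are tempting, and the article supports none of them.

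- *These two rows ignore the cluster allocation while the other outcomes' models account for it.* The linear mixed models are said to handle correlation from repeated measurements at t1–t4. No outcome is given an admission-cluster term, so clustering is a question for the whole trial. These rows differ from the mixed-model rows only on missing data: a t-test drops anyone without the outcome, where 30% dropout is expected.
- *The sick-day comparison is biased by the 3-week absence.* Both arms have it, and a constant cancels. Harm would need inconsistent reporting, and nothing shows that. The questionnaire wording is not shown and may already settle what is counted.
- *Sick days need a count model because they are skewed.* At about 100 per arm the t-test keeps its level; a negative binomial model is an option.

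The article also says that the self-reported work outcome will be interpreted with caution, and its Quasi-randomisation limitations foresee adjustment, for example if baseline is imbalanced. Neither statement names a method for employment status, so neither repairs that row.

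**Conclusion.** The point holds for employment status: the stated test does not fit the outcome as the article describes it. It would be approximately valid only under a 0/1 coding that is nowhere defined. The range of 0.009 to 0.859 illustrates the dependence on numbering under assumed counts. It is not a forecast for this trial, and it does not mean that every p-value is attainable.

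For sick days the planned test is acceptable. What remains is interpretation, because the outcome is conditional on having work, and one open definition, whether the planned absence counts. Counted consistently, that absence does not bias the comparison. Both outcomes are secondary; the primary analysis and the sample size of 286 are untouched.

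**What to change.** 1. In the employment row of Table 2, replace the t-test with a categorical method. One option is in work at t4 (yes/no) by logistic regression or a logistic GLMM, adjusted for t1 employment status and reported as a risk difference with its confidence interval. If the categories are kept, name them and use a chi-square test or a multinomial model.
2. Report sick days directly beside the employment result. Add a sensitivity analysis among those employed, labelled as supportive because it selects on a status observed after allocation.
3. State whether the 3-week absence after discharge counts as sick days. If the questionnaire already settles this, quote its instruction.

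The first two changes cost analysis wording only, since employment status is collected at baseline and is itself an outcome. The third is one sentence. Rewording the sick-day item now is not advised: recruitment began on May 13, 2025, and a change midway could leave two definitions in one dataset. An offset for days employed is not requested either, because it may need data that the article does not list.

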### Objectives {7}

Accordingly, this study aims to determine the impact of a maintenance programme—comprising an individual goal-setting interview and the use of the MiA app—on the skin protection behaviour of patients with WRHE. Skin protection behaviour in this context includes the implementation of skin protection, cleansing, and care measures in both occupational settings and private daily life. We hypothesise that the aforementioned interventions will lead to a statistically significant improvement in the adoption and maintenance of appropriate skin protection behaviour, with an expected effect size in the lower range between small and medium. Further objectives are to evaluate the effect on the skin condition of the hands, action control, HRQoL, employment status, as well as the number of days of sickness-related absence from work due to the skin condition over the follow-up period.

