## Assignment of interventions: allocation

### Sequence generation {16a}

Participants will be allocated to either the intervention or control group in clusters based on their admission date at the clinic, following a predetermined quasi-randomisation allocation scheme. The assignment to the intervention or control group is thus planned prior to the start of the study. This pragmatic approach is justified for several reasons: firstly, patients will participate in a 3-week inpatient maintenance programme. Given the duration of their stay and the potential for interpersonal interactions, it is essential to incorporate designated wash-out periods to prevent contamination between groups. Additionally, participants will be allocated in clusters rather than at the individual level. Therefore, to ensure the study is completed within an appropriate timeframe, no alternative method of random group allocation is feasible. Furthermore, to minimise potential confounding due to seasonal factors and occupational patterns, the allocation scheme ensures that participants in both groups are recruited continuously throughout the entire year. This is important because climatic influences (such as winter cold) and the seasonal admission of certain occupational groups (e.g. construction workers more often admitted in winter) may affect outcomes; thus, both groups are exposed to these factors equally.

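### Table 2 prescribes a two-sample t-test for employment status, a categorical outcome with a recorded baseline value that the test does not use

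*Protocol article*

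**What the plan says.** Objectives {7} lists employment status among the effects to be evaluated: "action control, HRQoL, employment status, as well as the number of days of sickness-related absence from work". Outcomes {12} makes it a secondary outcome: "Employment status and number of days of sickness-related absence from work (due to the skin condition) during the follow-up period". No categories, coding or single time point are given there.

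Plans for assessment and collection of outcomes {18a} records the same variable at entry: "At baseline, the following sociodemographic data will be collected: age, sex, current occupation, highest educational qualification, employment status, and relationship status". That section adds that secondary outcomes are also assessed at baseline.

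The analysis is fixed in Table 2 under Statistical methods {20a}. The row for employment status reads "Descriptive; two-sample *t*-test", the same entry as for sick days. The text of {20a} names the linear mixed model as preferred for primary and secondary outcomes, and Table 2 gives the ordinal school grade a generalised linear mixed model.

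On comparability, Outcomes {12} says of this group of self-reported outcomes that "no relevant confounding that would impair the comparability between groups is anticipated". The limitation headed Quasi-randomisation says that confounding may influence observed effects and that the design is open to allocation and selection bias. It plans adjustment analyses, for example if baselines are imbalanced, without naming outcomes or covariates.

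**The concern.** Employment status is a category, and a t-test needs a quantity whose mean has a meaning. The row names a specific test, so this is a stated choice and not a detail left to an analysis plan. It goes wrong in one of two ways, depending on a coding that the article does not give.

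- **Three or more nominal categories** (for example employed, self-employed, in retraining, unemployed): the test compares average code numbers, and the result depends on the numbering.
- **Yes/no coding:** the test is acceptable as a comparison of two proportions, but it ignores who was already out of work at admission. Status at entry is likely to be a strong predictor of status at 6 months. Groups formed by admission date, with allocation known before consent, need not start level on it.

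At stake is the credibility of one stated objective. A real shift between categories could be missed, or a difference present at admission could be read as an effect of the programme.

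**Working it through.** **The plan's own figure.** The article gives no calculation for employment status. The sample size for the primary outcome reproduces: d = 0.4, two-sided alpha 0.05 and power 0.80 need 99.08 per arm, rounded up to 100; 200 / 0.70 = 285.7, rounded up to 286. The illustrations below use 100 patients per arm. All employment rates in them are assumptions.

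**Step 1: three or more categories.** Take four categories with counts 70/10/5/15 in one arm and 60/10/25/5 in the other. The mean code is the sum of (code × count) / 100.

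| Codes given to the four categories | Mean, arm 1 | Mean, arm 2 | t-test p |
|---|---|---|---|
| 1, 2, 3, 4 | (70+20+15+60)/100 = 1.65 | (60+20+75+20)/100 = 1.75 | 0.50 |
| 4, 1, 3, 2 | (280+10+15+30)/100 = 3.35 | (240+10+75+10)/100 = 3.35 | 1.0 |
| 2, 3, 4, 1 | (140+30+20+15)/100 = 2.05 | (120+30+100+5)/100 = 2.55 | 0.00002 |

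The last two rows are the extremes over all 24 orderings. Chi-square on 3 degrees of freedom gives 19.1, p = 0.0003, whatever the numbering. A milder table, 70/10/12/8 versus 58/10/26/6, gives t-test p-values from 0.015 to 0.54 against one chi-square answer of 0.087.

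**Step 2: yes/no coding, level baselines.** With 90% versus 80% in work, the t-test gives p = 0.0480 and uncorrected chi-square 0.0477. With 80% versus 68%, the values are 0.0534 and 0.0531. The simulated type I error of the t-test is 0.043 to 0.052 for true rates from 70% to 95%. The coding problem disappears.

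**Step 3: yes/no coding, unequal baselines, no treatment effect.** Let b be the proportion in work at entry, s the proportion of those in work who still are at 6 months, and r the proportion of those out of work who have returned. The 6-month rate is b·s + (1 − b)·r, so the spurious difference between arms is (b₁ − b₂)(s − r).

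With s = 0.88 and r = 0.25:

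- 85% versus 92% at entry: −0.07 × 0.63 = −0.044 (78.6% versus 83.0% at 6 months). The t-test rejects in 12.6% of simulated trials.
- 80% versus 92% at entry: −0.12 × 0.63 = −0.076 (75.4% versus 83.0%). It rejects in 26%.

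These treat the entry rates as those of the populations admitted. If exactly 85 and 92 (or 80 and 92) of 100 patients are in work at entry, the rejection rates are 9% and 23%.

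Over a wider range, with imbalances of 5 to 10 points, s from 0.80 to 0.90 and r from 0.10 to 0.40, the spurious difference is 0.05 × (0.80 − 0.40) = 2 points up to 0.10 × (0.90 − 0.10) = 8 points.

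**Step 4: the alternative.** In the two main scenarios of Step 3, a logistic regression on group and baseline status rejects in 5.1% and 5.7% of 1,500 simulated trials each, which is the nominal level within simulation error.

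**The case against.** The coding is not given, and an article may leave it to a fuller document. If status is recorded as working or not, the t-test is a sound approximate test of proportions. That stands, and it makes the first half of the point conditional. The second half remains: a two-sample t-test has no place for a baseline term.

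The Quasi-randomisation limitation foresees adjustment for baseline imbalance, so it would be wrong to say that the whole plan ignores status at entry. But that provision is conditional and names neither outcome nor covariate, while Table 2 names the test.

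This is also one secondary outcome without a power claim, and Outcomes {12} promises cautious interpretation. That limits the weight of the point.

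Three stronger readings are tempting and are not supported:

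- **That the test is run on 6-month responders only.** The row names no time point or responder set. Patients without a follow-up value would in practice drop out of a t-test, but the article does not define the analysis that way.
- **That it breaches the intention-to-treat statement.** That statement is "all randomised participants will be analysed in the groups to which they were originally assigned", regardless of adherence. It concerns group membership and is compatible with a t-test. A logistic regression at 6 months would likewise omit patients without follow-up data, so missing data do not decide between the two.
- **That Outcomes {12} contradicts Sequence generation {16a}.** The latter says that "the seasonal admission of certain occupational groups (e.g. construction workers more often admitted in winter) may affect outcomes", but its sentence concludes that both groups are equally exposed, because both are recruited throughout the year. It supports the expectation in {12}. The tension is with the Quasi-randomisation limitation.

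**Conclusion.** The point holds in a limited form. The t-test is the wrong tool if employment status has three or more nominal categories. If it is yes/no, the test is valid in form but inferior, because it discards a baseline value that the trial collects, in a design whose authors concede possible confounding.

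Under the assumed rates, ordinary-looking baseline differences produce spurious differences of roughly 2 to 8 points, and false-positive rates of about 13% to 26% in the two main scenarios. These sizes rest wholly on assumed employment, retention and return rates; with level baselines the excess vanishes. Neither the primary outcome nor the sample size of 286 is affected. The change should be made, but nothing else in the trial depends on it.

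**What to change.** In the employment row of Table 2:

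1. Define the status to be tested (for example, in paid work yes/no) and the time point (6 months after discharge).
2. Replace the t-test by a logistic regression of that status on group and employment status at t1. If status is measured at more than one follow-up point, a logistic mixed model is an option. It should leave out the assessment around discharge (t2), when patients are off work by design. The participant timeline is not legible in the text at hand, so repeated measurement cannot be assumed.
3. Report the difference in proportions and the odds ratio with 95% confidence intervals, and list the full categories descriptively.

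In Outcomes {12}, reconcile the sentence on confounding with the Quasi-randomisation limitation.

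The cost is one table row and one sentence. The baseline value is already collected, and recruitment runs to about October 2026, so the change can precede the analysis. If few patients are out of work, the model must stay sparse: group and baseline status, with little else.
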